### Sample size

Based on the chosen primary outcome measure, Infant Motor Profile (IMP [31],), and on IMP results of a pilot study and of previously conducted RCT in preterm infants without congenital brain lesions [15, 19, 20] and considering a 80% power and a significant level of 0.05 and a effect size of at least 0.6, a sample of 38 children is required. However, considering also a 10% of drop-out rate, a minimum of 42 infants will be required. In order to facilitate parental work and participation in the project, eligible twins will be allocated into the same group.

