**Methods/design:**

This RCT will be multi-centre, paired and evaluator-blinded. Eligible subjects will be preterm or full-term infants with brain lesions, in first year of age with predefined specific gross motor abilities. Recruited infants will be randomized into CT-R and IM groups at baseline (T0). Based on allocation, infants will perform an 8-week programme of personalized CareToy activities or Infant Massage. The primary outcome measure will be the Infant Motor Profile. On the basis of power calculation, it will require a sample size of 42 infants. Moreover, Peabody Developmental Motor Scales-Second Edition, Teller Acuity Cards, standardized video-recordings of parent-infant interaction and wearable sensors (Actigraphs) will be included as secondary outcome measures. Finally, parents will fill out questionnaires (Bayley Social-Emotional, Parents Stress Index). All outcome measures will be carried out at the beginning (T0) and at end of 8-weeks intervention period, primary endpoint (T1). Primary outcome and some secondary outcomes will be carried out also after 2 months from T1 and at 18 months of age (T2 and T3, respectively). The Bayley Cognitive subscale will be used as additional assessment at T3.

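### The stated 38 evaluable infants for 80% power at effect size 0.6 do not fit the planned comparison of two independent arms; 38 matches a one-sided paired t-test that the protocol does not describe

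*Protocol article*

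**What the plan says.** The Sample size section bases the number on the Infant Motor Profile (IMP), drawing on IMP results from a pilot study and an earlier trial in preterm infants without brain lesions. It gives the operating figures as "considering a 80% power and a significant level of 0.05" and concludes: "a effect size of at least 0.6, a sample of 38 children is required". It then adds losses: "considering also a 10% of drop-out rate, a minimum of 42 infants will be required". The Abstract repeats the result: "On the basis of power calculation, it will require a sample size of 42 infants". The section gives no test, sidedness, standard deviation or definition of the effect size.

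Four other parts of the article bear on which test the number should serve:

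- The Abstract and the Study design section both call the trial paired. Neither names a matching factor.
- The Randomisation section assigns participants 1:1 from sealed, numbered envelopes, with no mention of forming pairs.
- The Sample size section places eligible twins in the same group.
- The Analyses section calculates T1 minus T0 change and compares CT-R with IM. The covariates are baseline motor level, type and grade of brain lesion, family compliance and dose of intervention. No within-pair analysis is described.

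**The concern.** The four printed figures (power, significance level, effect size and number) should belong to the comparison the trial will make. As described, that is a difference in mean change between two independent groups of about 19. An effect of 0.6 standard deviations is moderate, and 19 per group is far fewer than such a comparison usually needs at 80% power.

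If the number comes from a different test, readers are promised power that the primary comparison may not have. A non-significant result would then carry less information than the stated 80% suggests. This matters because the Background presents IM as a sound alternative to CT-R, so a null result could be taken to mean that the two are equally good.

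**Working it through.** **Inputs.** From Sample size: power 80%, significance level 0.05, effect size d = 0.6, 38 evaluable, 10% drop-out, 42 enrolled. From Randomisation: 1:1, so 19 evaluable per arm. Sidedness is not stated, so both versions are run. Normal quantiles: 1.960 (two-sided 0.05), 1.645 (one-sided 0.05), 0.842 (80% power).

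**Step 1: reproduce 38.** For a paired test, the number of pairs is n = ((z_alpha + z_beta)/d)².

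- One-sided: ((1.645 + 0.842)/0.6)² = 17.2. With the t distribution it is 18.6, so 19 pairs, or **38 infants**, which is the stated figure. Check: noncentrality 0.6 × √19 = 2.615, 18 degrees of freedom, critical value 1.734, power 80.8%.
- Two-sided: ((1.960 + 0.842)/0.6)² = 21.8. With the t distribution it is 23.8, so 24 pairs, or 48 infants. With 19 pairs the critical value is 2.101 and power is 69.6%.

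**Step 2: number for two independent arms.** Per arm, n = 2 × ((z_alpha + z_beta)/d)².

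- Two-sided: 2 × 21.8 = 43.6. With the t distribution it is 44.6, so 45 per arm, **90 in total**.
- One-sided: 2 × 17.2 = 34.4. With the t distribution it is 35.04, so 36 per arm, **72 in total**.

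Neither version gives 38.

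**Step 3: power of 38 in two independent arms, unadjusted.** Noncentrality is d × √(n/2) = 0.6 × √9.5 = 1.849, with 36 degrees of freedom.

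| | Critical value | Power, 19 per arm | Power, 21 per arm | d detectable at 80%, 19 per arm |
|---|---|---|---|---|
| Two-sided | 2.028 | 43.7% | 47.5% | 0.93 |
| One-sided | 1.688 | 56.7% | 60.5% | 0.82 |

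**Step 4: what covariates could add.** Suppose 0.6 is in units of the raw IMP standard deviation and the analysis adjusts for baseline. The effective size is then 0.6/√(1 − r²), where r is the T0 to T1 correlation (35 degrees of freedom). The article gives no r, so a range is shown.

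| Assumed r | Effective d | Power two-sided | Power one-sided |
|---|---|---|---|
| 0.5 | 0.69 | 55% | 67% |
| 0.7 | 0.84 | 71% | 81% |

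Power reaches 80% at r of about 0.77 two-sided (r² about 0.59) and about 0.68 one-sided (r² about 0.47). If 0.6 is already standardised on the change score, and the covariates explain nothing further, Step 3 applies unchanged.

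**Step 5: drop-out.** 42 × 0.9 = 37.8, so 42 enrolled leaves about 38. Dividing instead, 38/0.9 = 42.2. The difference is one infant and does not matter here.

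**The case against.** The strongest defence is that the article twice calls the trial paired, and 38 is exactly what a paired calculation gives. On that reading the number is internally reproducible. What stands is that the paired label explains where 38 probably came from. It does not support the figure for the trial as described. No matching factor is named, the envelopes hold plain 1:1 sets, and no within-pair analysis is planned. Twins, the one natural pairing, go to the same arm and so cannot form CT-R/IM pairs. Even with genuine pairs, 38 reaches 80% only with a one-sided test, which is stated nowhere.

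A second defence is that the Analyses section plans covariates, including baseline motor level and brain lesion, that may raise precision. This is fair, and Step 4 shows that 38 could suffice. It requires a high correlation, which the article neither states nor supports.

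A third is that an article may leave the test and its sidedness to a fuller document. That is accepted, and the silence alone would be no finding. The point is that the figures the article does print do not fit the design it does describe.

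Three stronger readings are tempting and are not supported:

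- A reader might infer that the trial simply has 44% power. That figure requires two-sided testing, 0.6 in units of the analysed outcome's standard deviation, and no covariate gain. The article settles none of these.
- A reader might infer that a null result is more likely than not even if the effect is real. Among the cases computed, this holds only for the unadjusted two-sided one; the others lie above 50%.
- A reader might treat the drop-out step as an error. It is a rounding matter, and 42 is given as a minimum.

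**Conclusion.** The concern holds in a limited form. The combination of 80% power, 0.05, effect size 0.6 and 38 evaluable infants is not supported for the between-arm comparison of change that the article describes. An unadjusted comparison of independent arms needs 90 infants two-sided or 72 one-sided, about twice the stated number on either reading. With 19 per arm, its power is about 44% or 57%.

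The actual power is undetermined, not shown to be any single value. It depends on sidedness, on the units of the 0.6, and on how much the covariates explain. It reaches 80% only with a one-sided matched-pair analysis, or with a T0 to T1 correlation of about 0.77 (two-sided) or about 0.7 (one-sided) and 0.6 read in raw-score units. The article states none of these conditions. The calculations assume equal arms, equal variances and independent infants. Twins in the same arm would, if anything, reduce the information slightly.

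**What to change.** Reword the Sample size section; recruitment need not change.

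1. Reconcile the paired label in the Abstract and Study design with Randomisation and Analyses. Either state the matching factor and the within-pair analysis, or drop the label.
2. Name the test, its sidedness and the definition of the effect size, including which standard deviation it uses.
3. Restate the power to match. For two independent arms, two-sided and unadjusted, the text could read: *42 infants (about 38 evaluable, 19 per arm) give 80% power for a standardised between-group difference of about 0.93, and about 44% for 0.6.*
4. If covariate adjustment is relied on, state the assumed correlation and the power that follows from it.

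The cost is a few sentences. The downside is that the stated power becomes less favourable unless a matched analysis or a high correlation can be justified.

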### Randomisation

Randomization will be done after enrolment: participants will be randomly assigned to CT-R training or IM group by the use of an automatic generation of 1:1 sets. A third party blind to clinical aspects of trial will manage these sets, sealing them in numbered envelopes.

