### Analyses

Statistical Package for Social Sciences (SPSS) will be adopted for carrying out the statistical analyses. Descriptive statistics will be performed to create the record of the data for each group. Potential baseline differences and between group differences will be explored computing the *p* values. When necessary, Bonferroni correction will be applied. Firstly, delta changes immediately after treatment (T1, primary endpoint) vs baseline will be calculated to assess the short-term effects of CT-R training versus IM in primary and secondary outcome measures, taking account as covariates base level of motor development, type and grading of brain lesion, family compliance and dose of intervention. After, multivariate statistics will be performed.

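### Twins share an arm, but the sample size and the stated analysis make no allowance for family clustering; if correlated pairs enrol, standard errors are too small

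*Protocol article*

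**What the plan says.** Under Sample size, the protocol article sets the target by "considering a 80% power and a significant level of 0.05 and a effect size of at least 0.6" and concludes that "a sample of 38 children is required". It then allows for attrition: "considering also a 10% of drop-out rate, a minimum of 42 infants will be required". The last sentence of that paragraph adds, for the convenience of parents, that "eligible twins will be allocated into the same group". Dropout is the only adjustment made to the number of children.

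Under Randomisation, the general rule is that "participants will be randomly assigned to CT-R training or IM group by the use of an automatic generation of 1:1 sets", with the sets sealed in numbered envelopes. How a twin pair draws from those envelopes is not described.

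Under Analyses, "delta changes immediately after treatment (T1, primary endpoint) vs baseline will be calculated" for the primary and secondary outcomes. The comparison between arms is adjusted for baseline motor level, type and grade of brain lesion, family compliance and dose of intervention. Unspecified multivariate statistics follow. No family or twin effect is named.

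**The concern.** When co-twins must go to the same arm, one random draw decides the treatment of two infants. Their outcomes are likely to be more alike than those of two unrelated infants. They share gestation and home, the parents who deliver the training or massage, and the parents who complete the Parenting Stress Index and the Bayley Social-Emotional scale. Two positively correlated infants in one arm carry less information than two independent ones. A comparison that ignores this understates the variance of the treatment difference.

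Two things are at stake. The first is the validity of the p-value and confidence interval for the Infant Motor Profile at T1, and probably more so for the parent-completed scales. The second is power: a sample counted in children delivers less than it appears to. In a trial of 42 infants, a borderline result would be open to challenge on this ground.

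**Working it through.** **Inputs from the protocol article (Sample size, Randomisation).** 38 evaluable children, 42 with 10% dropout, 80% power, significance level 0.05, effect size 0.6, 1:1 allocation, co-twins in the same arm.

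**Inputs not in the article, assumed here.** Number of enrolled twin pairs *k* from 1 to 8 among the 38 evaluable infants; residual within-pair correlation ICC from 0.3 to 0.8.

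**Step 1: the plan's own figure.** The dropout step reproduces: 38 × 1.10 = 41.8, so 42 (38/0.90 would give 43). The 38 itself does not follow from a two-sided, two-arm comparison at a standardised difference of 0.6, which needs about 44 per arm, 88 in all. It can be approached only by adding assumptions that the article does not state, such as a one-sided paired test (19 pairs) or adjustment for a baseline correlated about 0.75 with the outcome (88 × (1 − 0.75²) = 38.5). That is a separate matter. What counts here is that none of these routes to 38 or 42 contains an allowance for twins.

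**Step 2: design effect.** Let *f* be the share of infants who have an enrolled co-twin, *f* = 2*k*/38. Then

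- design effect DE = 1 + *f* × ICC
- effective sample size = 38/DE
- approximate true two-sided type I error of the unadjusted comparison = 2 × [1 − Φ(1.96/√DE)]
- power of a valid analysis, taking the stated 80% at face value = Φ((1.96 + 0.84)/√DE − 1.96)

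The last column simulates an ordinary two-sample t-test with families randomised and no treatment effect (N = 38, 40,000 runs per row).

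| Pairs | *f* | ICC | DE | Effective n | Type I error, formula | Power | Type I error, simulated |
|---|---|---|---|---|---|---|---|
| 0 | 0 | any | 1.00 | 38 | 5.0% | 80% | not run |
| 1 | 0.053 | 0.3 | 1.016 | 37.4 | 5.2% | 79% | 5.1% |
| 1 | 0.053 | 0.8 | 1.042 | 36.5 | 5.5% | 78% | 5.5% |
| 2 | 0.105 | 0.3 | 1.032 | 36.8 | 5.4% | 79% | 5.3% |
| 2 | 0.105 | 0.8 | 1.084 | 35.0 | 6.0% | 77% | 5.9% |
| 4 | 0.211 | 0.3 | 1.063 | 35.7 | 5.7% | 78% | 5.8% |
| 4 | 0.211 | 0.5 | 1.105 | 34.4 | 6.2% | 76% | 6.1% |
| 4 | 0.211 | 0.8 | 1.168 | 32.5 | 7.0% | 74% | 7.1% |
| 8 | 0.421 | 0.3 | 1.126 | 33.7 | 6.5% | 75% | 6.4% |
| 8 | 0.421 | 0.8 | 1.337 | 28.4 | 9.0% | 68% | 9.1% |

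**Step 3: scale against the dropout allowance.** In the middle case of 4 pairs and ICC 0.5, keeping the intended information needs 38 × 1.105 = 42.0 evaluable infants. The twin effect alone would then use up the whole margin set aside for dropout.

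**Limit of the check.** The t-test stands in for a covariate-adjusted comparison of change scores. The ICC in the table should therefore be read as the correlation that remains after adjustment.

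**The case against.** The strongest reply has four parts.

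*The analysis half rests on silence.* The Analyses section never says that infants are independent and fixes no variance estimator. An analysis plan that is not shown could add a family effect. This stands as far as it goes: a reader might infer that the trial will report a type I error above 5%, and the article does not establish that. The reply does not reach what the article does fix, which is the co-allocation rule and a sample size that takes no account of it. A later family effect would repair the p-value but not restore the power. The article also goes as far as naming its covariates, and the cluster that it created is not among them.

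*The number of pairs may be very small.* Eligible infants may be preterm or full-term. Both co-twins must meet the lesion and neurological criteria, still be abnormal at 2–3 months, and fall within the motor window. None, one or two enrolled pairs is plausible. This stands, and it is why the range runs down to negligible inflation.

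*The residual correlation may be modest.* The outcome is a change score adjusted for baseline motor level, lesion, compliance and dose, some of which co-twins may share. This also stands; it argues for the lower ICC values, not for zero.

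*The Randomisation section is not a contradiction.* A reader might set "participants will be randomly assigned to CT-R training or IM group" against the twin rule. The twin sentence is better read as an exception to that general wording. What is missing is only how the exception is carried out.

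**Conclusion.** The point holds conditionally. The article makes the family the randomised unit for twins and carries this into neither the number of children nor the stated comparison. If correlated pairs are enrolled and the comparison is run as worded, standard errors are too small. With 1 to 8 pairs among 38 infants and a residual ICC of 0.3 to 0.8, both assumed, the design effect is about 1.02 to 1.34, the effective sample size about 37 to 28, and type I error about 5% to 9%. The upper end needs 16 of 38 infants (42%) to be twins with an ICC of 0.8 and is not a central expectation. With one or two pairs, type I error stays at or below about 6%.

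The documents do not support an unconditional statement that type I error exceeds 5%, because they give no twin share and no correlation. They do support changing the plan, since the rule that creates the clustering is already fixed and the correction is cheap.

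**What to change.** 1. **Randomisation:** state that twins are randomised as a family, with one envelope per family.
2. **Analyses:** analyse every outcome with family as the cluster, singletons being families of one. Use either a linear mixed model with a family random intercept and small-sample degrees of freedom (such as Kenward-Roger), or cluster-robust standard errors with a small-sample correction.
3. **Fallback:** prespecify what is done if the family variance cannot be estimated. The need is real: in a simulation with 2 pairs and ICC 0.5, the within-pair residual cross-product was zero or negative in about 27% of runs, so a random intercept would tend to collapse towards the unadjusted model. One option is to analyse one randomly chosen infant per family as a sensitivity analysis.
4. **Sample size:** give the expected share of twins *f* and an assumed ICC, state that the effective sample size is 38/(1 + *f* × ICC), and acknowledge that power is somewhat below the stated 80%, or raise the target by the same factor.

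The first three are changes of wording, and co-allocation of twins for the parents' convenience is kept. The price is slightly wider confidence intervals and a slightly less favourable stated power. Stating the reduced effective sample size does not win back power; only more infants would.

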### Randomisation

Randomization will be done after enrolment: participants will be randomly assigned to CT-R training or IM group by the use of an automatic generation of 1:1 sets. A third party blind to clinical aspects of trial will manage these sets, sealing them in numbered envelopes.

### Blinding

Parents, therapists and clinical staff will be aware about the allocation group of infants. Assessors who will evaluate infants with outcome measures (IMP; Peabody Developmental Motor Scales - Second Edition (PDMS-2); Bayley Scales of Infant Development III Edition, BSID-III) will use the video-recording of the assessment session so they will be absolutely blind.

### Therapy protocols

#### CareToy-R training

As in a previous study [20], the clinical staff, mainly composed by child neurologists and paediatric physical therapist will organize customized goal-directed rehabilitative activities (i.e. CareToy scenarios) to be done in three different possible position which could be sitting, supine or prone, mainly focused on: postural abilities (e.g. postural control, rolling...), manipulation capabilities (e.g. reaching, grasping, manipulation…) and visual functions (e.g. visual attention and orientation…).

The new CT system, i.e. the revised version (CT-R), has been planned and designed in order to adapt the CareToy system to this new population by integrating a support for posture maintenance. Based on postural needs of brain-lesioned infants, a modular system called Siedo & Gioco (Fumagalli, Italy) has been incorporated. Siedo & Gioco system is a soft multifunctional system which allows the infant or a small child to be placed in many different confortable and safe positions (e.g. supine, prone, sitting or on one side). The Siedo & Gioco system is composed a set of soft and coloured modules with different shapes which can be attached to a mat by Velcro straps placed on modules and on mat. Technical specification for optimize suitability of Siedo & Gioco to CT system have been provided and an ad-hoc set of modules has been created in order to offer postural and perceptive stimuli. Thanks to the flexibility of this integrated system, the modularity of CT platform in this revised version (CT-R) has been maintained.

According to the initially established activities and modules (the activities and consequently the modules will be periodically updated), the CT-R system will be customized and delivered to the family’s home. CT-R training will be structured in 8 weeks, in which there will be about 30–45 min of daily planned activities, consisting of different scenarios lasting 2–10 min each.

Parents will be instructed to carry out the daily training during the wake and active periods of their infants. It will be remotely supervised by the clinical staff, who will have the possibility to remotely manage the CT scenarios based on each infant rehabilitation requirement and improvement during the 8-weeks training. Each scenario will be scored at the end by the parents on the basis of a questionnaire recording the infant’s acceptance and compliance.

Rehabilitation staff will train parents to use the system and to interact with their infant during the first 5 days of training and once a week in the following weeks.

#### Infant massage

Infant massage consists generally of a systematic touching by hands on different parts of the body and is characterized by slowness and gentleness [22]. IM is often associated to other forms of “contact” with the infant, e.g. kinaesthetic (arm and leg passive extension/flexion), auditory, verbal or visual stimuli.

Families assigned to IM group will perform a training course of 4–5 sessions lasting about one hour each. The massage will be done on different body areas and illustrated material on how to perform massage sessions at home will be provided to families. Parents will be required to perform IM 5 days a week, depending on the child’s willingness, for 8 weeks, and to record massage frequency in a dedicated diary.

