### Intervention phase

In the interventional phase, infants will proceed with an early intervention, which could be CareToy-R or Infant Massage, according to allocation group. Each intervention will last 8 weeks, 5 days a week; during this experimental phase all infants will continue to receive standard care foreseen by National Health System. All other specific interventions (such as physical therapy or other treatments) will be recorded in a specific diary. Therapy protocols are described below.

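### As the records are described, dose can be compared between CT-R and Infant Massage only as days or sessions performed, so a difference in time delivered would not show

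*Protocol article*

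**What the plan says.** All references are to the protocol article.

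- **Both arms** (Intervention phase): "Each intervention will last 8 weeks, 5 days a week".
- **CT-R** (CareToy-R training): "there will be about 30–45 min of daily planned activities, consisting of different scenarios lasting 2–10 min each". On oversight: "It will be remotely supervised by the clinical staff". On the record kept at home: "Each scenario will be scored at the end by the parents on the basis of a questionnaire", which covers the infant's acceptance and compliance. Staff train the parents "during the first 5 days of training and once a week in the following weeks".
- **IM** (Infant massage): parents attend a course of four to five sessions of about an hour each. They then massage at home five days a week for eight weeks, as far as the infant is willing, and are asked "to record massage frequency in a dedicated diary". The section gives no length for a home massage and describes no staff contact after the course.
- **Analysis** (Analyses): the T1 comparison takes as covariates, among others, "family compliance and dose of intervention". The article does not define dose.

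**The concern.** The two arms match in weeks and in planned days per week. They are not described alike in time per day, in staff contact or in what is recorded at home. The Background states the purpose as comparing two kinds of early intervention, and it lists intensity among the features that such programmes need in order to work. The article itself therefore treats amount as a possible active ingredient.

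If CT-R does better at T1, a reader will ask whether the system did it, or more minutes of stimulation, or more coaching of the parents. Answering that needs time and contact recorded on the same scale in both arms. The IM record as described gives a count. The plan to use dose makes this more than missing detail: the article names a dose variable and describes, for one arm, a record from which time cannot be recovered.

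**Working it through.** The article states no total of hours or contacts, so there is no figure to reproduce. What follows is arithmetic on the stated schedules.

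**1. Planned training days, both arms.** 8 weeks × 5 days = 40.

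**2. Planned CT-R home time.** Days × minutes ÷ 60:
- 40 × 30 ÷ 60 = 20 h
- 40 × 45 ÷ 60 = 30 h

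**3. Planned IM home time.** 40 × m ÷ 60, where m is minutes per massage. The article gives no m, so the values below are assumptions. The last two columns divide 30 and 45 CT-R minutes by m.

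| Assumed m (min) | IM time (h) | CT-R/IM at 30 min | CT-R/IM at 45 min |
|---|---|---|---|
| 10 | 6.7 | 3.0 | 4.5 |
| 15 | 10.0 | 2.0 | 3.0 |
| 20 | 13.3 | 1.5 | 2.25 |
| 30 | 20.0 | 1.0 | 1.5 |
| 45 | 30.0 | 0.67 | 1.0 |

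The ratio runs from 4.5 to 0.67. CT-R could have several times the IM time, the same, or less.

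**4. What the frequency record would show.** A family that massages on every planned day records 40 of 40 in every row of the table. The entry does not distinguish 6.7 h from 30 h.

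**5. What the CT-R record would show.** Scenario scores, combined with planned scenario lengths, would let time be approximated. The article does not say that minutes delivered are recorded in this arm either.

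**6. Staff training contacts.** CT-R: 5 in the first five days, then one in each of the remaining 8 − 1 = 7 weeks, so 5 + 7 = 12, before any remote contact. IM: 4 to 5. The ratio of counts is 12 ÷ 5 = 2.4 to 12 ÷ 4 = 3.0.

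**7. Counts are not staff time.** The IM course amounts to about 4–5 h. The length of a CT-R contact is not stated. Twelve contacts would equal the IM course if they averaged 4 × 60 ÷ 12 = 20 min to 5 × 60 ÷ 12 = 25 min. Whether staff time differs, and by how much, cannot be read from the article.

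**8. Common scale.** Setting steps 4 and 5 side by side, the dose measure that both records support is days or sessions performed.

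**The case against.** The strongest reply is that the trial compares two programmes and makes no claim about type net of time or coaching. Intensity and remote management belong to what CT-R is. IM was offered partly so that every infant receives an intervention, and not as a time-matched control. This stands: the randomised comparison of the packages is valid, and unequal coaching may be intrinsic to CT-R. It limits the point to how a difference is explained.

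A second reply is that a condensed article may leave massage length and diary layout to the full protocol or the parents' material, and the definition of dose to the analysis plan. This stands in part. A planned length held elsewhere would still not record minutes delivered, and the record that the article does name is frequency.

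Some stronger readings are tempting, and the documents do not support them:

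- *That the diary holds nothing but frequency.* The article names frequency; it does not exclude other entries.
- *That dose is time in one arm and a count in the other.* Dose is undefined, and days or sessions out of 40 could serve both arms.
- *That CT-R infants receive more time.* The ratio in the table falls on both sides of 1.
- *That CT-R families receive 2.4 to 3 times the staff time.* Those are ratios of counts.
- *That CT-R supervision is continuous.* The article says it is remote and that staff are able to manage scenarios remotely.
- *That daily activities contradict a five-day week.* In "about 30–45 min of daily planned activities" the word reads naturally as per training day, within the five-day week set for both arms.

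**Conclusion.** The point holds in a limited form. With the IM record as described, the arms can be compared on days or sessions performed but not on time delivered. Planned CT-R home time is 20–30 h. IM time is unknown, and under assumed massages of 10 to 45 min the ratio lies between 0.67 and 4.5. Training contacts are 12 against 4–5 by count, with relative staff time unknown. These figures rest on the 40 planned days, on weekly CT-R contacts in weeks 2 to 8, and on the assumed massage lengths.

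A reader might infer that the trial cannot give a fair answer. It can: the effect of CT-R as delivered against IM as delivered is estimable. What the planned data could not support is attributing a difference to the type of intervention rather than to time or coaching. The point is worth acting on because the change is cheap and minutes not recorded during the eight weeks cannot be reliably recovered later.

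**What to change.** 1. Add minutes per massage to the IM diary beside frequency, and record CT-R minutes delivered in the same way.
2. Log staff contacts in both arms by number and length, including the IM course sessions and CT-R remote contacts.
3. Report minutes and contacts by arm beside the primary result.
4. Use minutes descriptively or in a sensitivity analysis, not as a covariate in the primary T1 comparison. Dose is measured after randomisation and is tied to arm, so adjusting for it could distort the randomised contrast. The Analyses section currently lists dose among the covariates, so that sentence needs amending.
5. Word the conclusion as CT-R as delivered versus IM as delivered.

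The cost is one more column in a diary that IM parents already keep, a matching record for CT-R, a staff contact log and one descriptive table. The burden on parents and staff is small. No change to either treatment schedule is proposed.
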